### Randomization

After completion of baseline data collection, participants are randomly assigned using a block randomization strategy. Twice as many participants will be randomized into the target intervention to allow us to power Aim 3 (primarily within group analysis). Block sizes of 3 or 6 will be randomly chosen and assignments balanced within each block to ensure balance over time. Randomization is revealed to participants by a nonblinded study coordinator.

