### Sample size and power calculations

The goal is to enroll 225 individuals into this trial, anticipating 20% drop-out. The trial was powered to detect intervention effectiveness (Aim 1). Assuming 180 participants complete the entire study with a correlation between repeat assessments of at least 0.4, alpha = 0.05 and a two-sided test, we will have over 80% power to detect a difference in slopes between baseline and immediately post-intervention as small as 0.5 standard deviations (SD). If alpha is reduced to 0.025 to account for the two primary outcomes, the minimum detectable difference in slopes is 0.54 SD. Our preliminary studies had a difference in slopes of 0.5–0.6 SD, although we expect the outcomes proposed for this study to be more sensitive to change in behaviors than those used in our preliminary studies.

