### Planned statistical analysis

#### Intervention effectiveness

To evaluate the success of randomization, we will first compare between interventions (structured, self-guided) on demographics and other variables using two-sample t-tests (continuous) and chi-square tests (categorical); Wilcoxon rank sum tests or Fisher’s exact tests will be used instead if assumptions are violated. If differences between intervention groups exist, follow-up analyses will include those variables as covariates to ensure any observed intervention effect is not due to other differences between the groups. Primary analyses will be intent-to-treat analyses, that estimate intervention effects based on groups as randomized. Due to the repeat assessments over time across individuals (baseline, immediately after the 6-month intervention, and at 6- and 12-months post-intervention), repeated measures, random effects models will be used to estimate differences in rate of change between the groups at different time points. The main intervention effect will be defined as the difference between groups from baseline to immediately after the 6-month intervention, although later time points will assess maintenance of those effects. These models will incorporate random intercepts and slopes to account for between-person variation in overall level and change over time. All model assumptions will be checked and transformations or repeated measures approaches for non-normal data, such as generalized estimating equation (GEE) approaches will be used if needed. List-wise deletion will be used if < 5% of the data are missing; multiple imputation will be used if > 5% of the data are missing. If data appear to be missing not at random or exceeds > 20% missingness (which we have put procedures in place to prevent), we will conduct sensitivity analyses using Wu-Carrol and Diggle-Kennward approaches that our team has previously applied in RCT trials [79, 80]. Similar analyses will be completed with the secondary outcome measures.

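### The list-wise deletion rule below 5% missing is unnecessary and, if applied per participant, conflicts with intent-to-treat; the missing-not-at-random sensitivity analyses are left discretionary at the planned drop-out

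*Protocol article*

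**What the plan says.** All the rules at issue are in the Protocol article, Planned statistical analysis, under Intervention effectiveness.

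- Analysis set: "Primary analyses will be intent-to-treat analyses, that estimate intervention effects based on groups as randomized".
- Model: repeated-measures random effects with random intercepts and slopes over four assessments (baseline, end of the 6-month intervention, and 6 and 12 months later). The main effect is the between-group difference from baseline to the end of the intervention.
- Missing data: "List-wise deletion will be used if < 5% of the data are missing; multiple imputation will be used if > 5" (per cent).
- Sensitivity: "If data appear to be missing not at random or exceeds > 20% missingness", the team will use the Wu-Carroll and Diggle-Kenward approaches. The article adds that procedures are in place to keep missingness from getting that high.

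Sample size and power calculations gives the expected attrition: "The goal is to enroll 225 individuals into this trial, anticipating 20% drop-out". That leaves 180 who complete the whole study.

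**The concern.** There are two separate problems.

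**List-wise deletion.** The term usually means removing a case that has any missing value. Someone with both the baseline and the end-of-intervention values who misses only a later visit would then leave the primary contrast. A likelihood random effects model needs no such step, since it uses whatever visits were observed and is valid under missing at random. The rule gives up randomised participants for no gain.

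**Triggers for the sensitivity analyses.** Observed data cannot separate missing not at random from missing at random, so the first trigger is a judgement made after the data are seen. The second is a cut-off that the planned drop-out reaches but does not pass.

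The structured arm has explicit activity goals and app tracking that the self-guided arm lacks, so outcome-related drop-out that differs by arm is plausible, although the article gives no arm-specific rates. A positive result could then be reported without any test of the assumption on which it depends.

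**Working it through.** **Inputs.** 225 enrolled, 20% drop-out, 180 completers, correlation at least 0.4, 0.5 SD at two-sided alpha 0.05, 0.54 SD at alpha 0.025 (Sample size and power calculations); 2:1 allocation (Randomization); four assessments (Study design). The timing of drop-out and how far drop-outs depart from missing at random are not given; both are assumed below and shown as ranges.

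**1. The plan's own figures reproduce.**
- Enrolment: 180 / (1 − 0.20) = 225.
- SD of change: √(2 × (1 − 0.4)) = 1.095.
- Standard error with 60 and 120 participants: 1.095 × √(1/60 + 1/120) = 0.173.
- Power at 0.5 SD, alpha 0.05: Φ(0.5/0.173 − 1.96) = 0.823 (0.819 with the t distribution). Stated: over 80%.
- Minimum detectable difference at alpha 0.025 and 80% power: (2.241 + 0.842) × 0.173 = 0.534 (0.538 with t). Stated: 0.54.

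**2. How many people the list-wise rule could remove.** The article does not say what the 5% is a percentage of.

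| Reading | Most that stays below 5% | Participants removed |
|---|---|---|
| Only missing visit rows are dropped | – | 0 |
| 5% of participants | 0.05 × 225 = 11.25, so 11 | up to 11 (4.9%) |
| 5% of visits, two missed per person | 0.05 × 900 = 45, so 44 | 44/2 = 22 (9.8%) |
| 5% of visits, one missed per person | 44 | 44 (19.6%) |

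The last row leaves 181 participants. With the same formula, power at 0.5 SD and alpha 0.05 is 0.825 with 181 and 0.898 with all 225. That gap assumes the missed visits fall after the end-of-intervention visit, so that all 225 have the primary contrast.

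Exactly 5% falls under neither rule.

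**3. Whether planned attrition passes the 20% cut-off.**
- By participants: 45/225 = 20.0%, which is not above 20%. The first count that is above it is 46 (20.4%). If each person drops out with probability 0.20, the chance of 46 or more is 0.46.
- By assessments, with 20% lost by month 18:

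| Assumed pattern | Missing at 0, 6, 12, 18 months (%) | Of all visits | Of post-baseline visits |
|---|---|---|---|
| All lost before month 6 | 0, 20, 20, 20 | 15% | 20% |
| Linear loss | 0, 6.7, 13.3, 20 | 10% | 13.3% |
| All lost after month 12 | 0, 0, 0, 20 | 5% | 6.7% |

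No entry exceeds 20%. With linear loss, final drop-out would have to exceed 0.20/0.50 = 40% (all visits) or 0.20/0.667 = 30% (post-baseline visits).

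**4. Illustration of what goes unchecked.** Assume structured-arm drop-outs do 0.5 SD worse than missing at random predicts and control drop-outs do not. The shift in the effect is the fraction missing at month 6 times 0.5 SD:
- linear loss: 0.067 × 0.5 = 0.03 SD;
- all lost before month 6: 0.20 × 0.5 = 0.10 SD, a fifth of the planned 0.5 SD.

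**The case against.** A reader might go further than the article allows in five ways.

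- **That the sensitivity check is switched off at 20% drop-out.** It is not. The triggers are joined by an or, so the judgement about missing not at random stays open. The check is discretionary, not excluded.
- **That intent-to-treat is broken in the scenario the trial was sized for.** List-wise deletion applies only below 5%. At 20% drop-out, multiple imputation would normally apply, and it keeps everyone randomised.
- **That whole participants are certainly deleted.** With one row per visit, deletion could mean only the missing row. The intent-to-treat sentence also speaks of grouping by allocation. Customary usage of both terms points the other way, but the fair criticism is of an ambiguous rule that conflicts under its usual meaning.
- **That 44 participants would be lost.** That needs 44 different people each missing one visit, with the 5% counted over all visits. Even then, power is at the level planned for 180 completers.
- **That bias of 0.10 SD is to be expected.** The 0.5 SD deficit is assumed, an equal deficit and equal drop-out in both arms would cancel, and the 180 are completers of the whole study, so fewer may be missing at month 6. Sessions are matched between arms and make-up sessions are offered.

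It can also be said that a condensed article leaves detail to the analysis plan. That covers items such as the size of a delta shift. It does not cover a deletion rule and triggers that the article itself states.

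**Conclusion.** The point holds in a limited form. The rule below 5% is unnecessary with the planned model and, if applied per participant, conflicts with intent-to-treat. Its cost ranges from no one, through 11 participants, to 44 of 225, with power of about 0.82 instead of 0.90 at that extreme. It belongs to the low-missingness branch.

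The missing-not-at-random analyses depend on a judgement the data cannot support or on a cut-off that planned attrition does not exceed: exactly 20% of participants, and about 5 to 15% of all assessments under the assumed drop-out patterns. At the attrition the trial expects, they are not guaranteed. The 0.03 to 0.10 SD shift illustrates what could go unexamined and is not an estimate of bias. This should be corrected, but it does not undermine the design or the stated sample size.

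**What to change.** 1. Delete the list-wise rule. Fit the likelihood random effects model to all observed data from all randomised participants, whatever the level of missingness.
2. Keep multiple imputation where it does work the model cannot: bringing in auxiliary variables, missing component tests in the cognitive composite, and the generalised estimating equations fallback, which without weighting or imputation is not generally valid under missing at random.
3. Remove both triggers. Run the Wu-Carroll and Diggle-Kenward analyses already named, or a delta-shift analysis applied by arm, unconditionally for both primary outcomes.

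The cost is a few sentences and one or two extra runs with methods the article says the team has used before. No change to sample size or data collection is needed.

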#### Characteristics of treatment responders

Initial analyses will be similar to those described above for Aim 1 only focusing on indicators of SDT (autonomy, competence, relatedness) and health literacy (HL) to assess change over time in these measures and whether those rates of change differ between intervention groups. In the next set of analyses, key outcomes include the primary and secondary outcomes. For SDT/HL measures that show no change over time for either intervention group and for the other characteristics only measured once (demographics), repeated measures, random effects models, will be used to assess how they are associated with change in trial outcomes (interaction between assessment and SDT indicators or other characteristics). Further interactions with intervention group will also be considered to evaluate differences in the association with change between groups. For SDT/HL measures that do show change, we will use an extension of the repeated measures, random effects called simultaneous modeling [81–83] that treats the variables with repeated measurements as outcomes, leading to multiple outcome variables in a single model. Combined, these analyses will allow us to test the hypothesis that certain sub-groups benefit more from the target intervention.

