### Study objectives

The overall objective of this study is to test, in a RCT, a multidomain intervention combining training in rehabilitation-based memory support strategies and lifestyle/health behavior modification on cognitive and functional outcomes. To capitalize on a critical window of opportunity to intervene, we will target cognitively normal older adults with SCD, an established ADRD risk. Two groups will be compared. The target intervention (referred to as the structured group) combines training in memory support strategies and healthy lifestyle modification and sets specific behavioral target goals that participants are encouraged to meet and actively track. It makes use of a senior-friendly Electronic Memory and Management Aid (EMMA) digital application [41, 42] to both build and support memory compensation strategies, and to support self-monitoring of healthy behavior goals, an important component in promoting health behavior change [43]. The structured intervention is theoretically grounded in Self Determination Theory (SDT [44, 45]), with an emphasis on building competency at a stage when cognitive functions remain intact, supporting autonomy through flexibility in choice of lifestyle changes (e.g., what type of physical exercise in which to engage), and support through a group-based intervention. This intervention will be compared to an education only group (referred to as the self-guided group) which provides similar information on compensation strategies and healthy lifestyles, but without providing explicit behavioral goals or support on how to implement the information**.** To meet the study objective, the following aims are planned: 1) evaluate intervention efficacy on primary outcomes including global measures of cognition and everyday function and secondary outcomes including target behaviors (increased compensation, increased physical and cognitive activity and enhanced stress management) and other important health outcomes (e.g., physical ability); 2) evaluate demographic and other characteristics of those who respond to the intervention to better understand for whom the intervention works; 3) evaluate treatment adherence and identify the components of the structured intervention that impact treatment success using a mixed-method approach that combines quantitative and qualitative data collection.

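### Aim 2: self-determination and health-literacy scales that change after randomisation are tested for association, not for who benefits more, and for the other characteristics the right interaction is only considered

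*Protocol article*

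**What the plan says.** The section Characteristics of treatment responders in the protocol article works in two steps. It first assesses whether each SDT indicator (autonomy, competence, relatedness) and health literacy changes over time, and whether that change differs by arm. The result then decides how the scale is related to the trial outcomes.

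- **No change seen, or measured once.** This branch opens "For SDT/HL measures that show no change over time for either intervention group and for the other characteristics only measured once (demographics". These characteristics enter random effects models as predictors through the "interaction between assessment and SDT indicators or other characteristics". The text then adds: "Further interactions with intervention group will also be considered to evaluate differences in the association with change between groups".
- **Change seen.** "For SDT/HL measures that do show change, we will use an extension of the repeated measures, random effects called simultaneous modeling". That model "treats the variables with repeated measurements as outcomes, leading to multiple outcome variables in a single model". No interaction with arm and no use of the baseline value is stated for this branch.

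The section ends: "Combined, these analyses will allow us to test the hypothesis that certain sub-groups benefit more from the target intervention". Under Study objectives, Aim 2 is framed as learning for whom the intervention works, and the article says: "The structured intervention is theoretically grounded in Self Determination Theory".

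**The concern.** A characteristic that identifies who benefits more has to be one the treatment cannot have altered, which in practice means its baseline value. Here, whether an SDT/HL scale is examined as a possible effect modifier depends on what happens to it after randomisation. The structured arm is built on SDT, so it is plausible that some of these scales will move. Those that do leave the branch in which an arm interaction is mentioned. They enter a model that relates two trajectories, either of which the intervention may have affected.

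In the other branch, the first term described is characteristic by assessment over both arms. It asks whether people with that characteristic change differently whatever they were assigned to, which is a prognostic question. Differential benefit needs the further interaction with arm.

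A prognostic factor, or a consequence of treatment, could therefore be reported as a responder characteristic and used to target later programmes. The Discussion names that use for the Aim 2 results.

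**Working it through.** **1. The plan's own figures.** The inputs from Sample size and power calculations are 180 completers, correlation 0.4 and two-sided alpha 0.05. Randomization gives 2:1 allocation, hence 120 and 60 completers.

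- SD of change = √(2 × (1 − 0.4)) = 1.095 baseline SD.
- SE of the arm difference in change = 1.095 × √(1/60 + 1/120) = 0.173.
- Power at 0.5 SD = Φ(0.5/0.173 − 1.96) = 82.3% (stated: over 80%).
- Minimum detectable difference at alpha 0.025 = (2.241 + 0.842) × 0.173 = 0.534 SD (stated: 0.54).

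The Aim 1 figures reproduce. The article gives no power figure for Aim 2.

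**2. How the sorting rule behaves.** The article gives no criterion for a scale showing change. Assume p < 0.05 within either arm, with correlation 0.4 for the scale as well.

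- No true change: the chance of going to the simultaneous model is 1 − 0.95² = 9.8%.
- True change of 0.2 SD in both arms: detection is 51.6% in the structured arm (n = 120) and 29.3% in the self-guided arm (n = 60). The chance of going to the simultaneous model is 1 − 0.484 × 0.707 = 66%.

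Under that assumption, the model applied to a modestly changing scale is partly a matter of chance.

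**3. What each term detects.** The simulation used 120:60 participants, an arm effect of 0.5 SD, residual SD of change 1.095 and 1,000 runs per scenario. Regression on change stood in for the longitudinal models. The effect sizes are assumptions.

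| Scenario | Characteristic × assessment | Arm × assessment × characteristic | Change on change |
|---|---|---|---|
| Prognostic only (0.3 SD per SD, both arms) | 94% | 5% | 4% |
| Modifier only (0.5 SD per SD, structured arm only) | 98% | 79% | 4% |
| Correlated changes (0.32 SD per SD within arm; scale raised 0.8 SD by treatment), no modification | 6% | 5% | 97% |

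The two-way term is significant almost as often for a purely prognostic characteristic as for a true modifier, so it cannot separate them. The change-on-change association is significant in 97% of runs when nobody benefits more than anyone else, and in 4% when a true modifier exists. Only the three-way term holds near 5% without differential benefit and responds when there is some.

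**4. What the three-way test can detect.** For a binary subgroup with share p, SE = 1.095 × √((1/p + 1/(1 − p)) × (1/60 + 1/120)). Alpha is 0.05 two-sided and power 80%.

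- p = 0.50 (assumed): SE = 2 × 0.173 = 0.346; detectable difference 2.802 × 0.346 = 0.97 SD; power at 0.5 SD about 30%.
- p = 0.25 (assumed): SE = 0.400; detectable difference 1.12 SD; power at 0.5 SD about 24%.
- Continuous moderator: SE about 0.173 per SD of the moderator; detectable difference about 0.49 SD per SD.

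**The case against.** A reader might infer that Aim 2 cannot say anything about which sub-groups benefit. The article does not support that. It names the correct interaction with intervention group for demographics and for every SDT/HL scale that does not change. Describing the two-way term first does not invalidate a later three-way term, and the arm interaction is not made conditional on the two-way result. What stands against the plan in this branch is only that the decisive test is left at "Further interactions with intervention group will also be considered".

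Several other points on the plan's side also hold:

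- The Discussion gives Aim 2 a second purpose, understanding which constructs an intervention can target. Joint modelling of a changing scale with an outcome serves that purpose.
- The simultaneous model extends the random effects models and could carry arm-specific terms; a fuller plan may say so. The point here is therefore confined to the sorting rule and the closing conclusion, both of which the article states.
- It is not certain that the SDT scales will change. Group format and contact are matched across arms, and the self-guided participants also shape their own programmes. Change is plausible, no more.
- A scale whose change goes undetected stays in the predictor branch, close to where it should be. The sorting percentages rest on an assumed p < 0.05 criterion.
- The article claims no power for Aim 2, so low power is not an error in it. Multiplicity control for a non-primary aim commonly sits in the analysis plan and is not raised here.

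The word combined in the closing sentence does not rescue the claim for scales that change. For those scales, no analysis described in the section tests an interaction with arm.

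**Conclusion.** The point holds in a limited form. For SDT/HL scales that are seen to change, the stated analysis gives association or possible mediation, and the conclusion that it helps test whether sub-groups benefit more is not supported. For demographics and unchanged scales the right test is named but given too little standing, behind a term that is prognostic.

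The risk is one of interpretation. Under the simulated assumptions, analyses that carry no information on differential benefit would be significant in 94% to 97% of runs. The exact percentages depend on the chosen effect sizes; that these terms do not test differential benefit does not. The change is worth making, but it concerns a secondary aim and leaves the Aim 1 analysis and sample size untouched.

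**What to change.** - For every SDT/HL scale and every demographic characteristic, use the baseline value, whether or not the scale later changes.
- Make arm by assessment by baseline characteristic the Aim 2 test of differential benefit. Report estimates with confidence intervals, and describe the results as exploratory.
- Keep the simultaneous models, label them association or mediation analyses, and draw no sub-group conclusion from them or from the two-way terms.
- Limit the closing sentence of the section to the three-way interactions.

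The cost is analysis wording and some additional model fitting. The article already plans to assess change over time in these scales, so no new data are needed. The drawback is the low power of the three-way test, shown above. Aim 2 should therefore be worded so that a non-significant interaction is not read as equal benefit.
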